### 9.2 Phase II

In the second part of the trial, the cohort of patients treated at the RD will be expanded, up to a total of 27 patients treated with vinorelbine 30 mg per square meter (days 1, 8 q21) plus sorafenib at the RD.

Six patients in this expanded cohort will undergo sample collection for pharmacokinetic analysis of vinorelbine and sorafenib.

### 9.3 Vinorelbine administration

Vinorelbine will be diluted in D5W or NS to a final concentration of 0.5-2 mg/mL, and administered as a 6-10 min infusion, through free-flowing IV, followed by an IV flush with 200 to 300ml NS or D5W.

Premedication (such as with dexamethasone, anti-nausea, or analgesics) will be according to internal directives for each center for the first administration, and then adjusted to each patient's need.

#### 9.4 Sorafenib administration

- Bayer will supply sorafenib tablets to the pharmacy in each clinic, that will ensure appropriate storage.
- Tablets will be dispensed only to subjects enrolled in this clinical trial, as 200 mg capsules (Nexavar®).
- Drug intake will be approximately every 12 hours (or every 24 hours in case of dose decrease to level -1).
- Patients can take sorafenib fasting.
- Skipped doses will not be recuperated.
- Subjects will be asked to return all unused tablets at the end of treatment.

#### 9.5 Duration of therapy

In both study phases, patients will receive up to a total of 8 cycles of combination therapy with vinorelbine and sorafenib, unless disease progression or unacceptable toxicity is manifested, or a patient withdraws informed consent.

In case of late response, patients can receive more than 8 cycles of combination therapy, up to 4 cycles after achievement of the best response obtained.

After completion of the combination therapy, those patients whose disease has not progressed during the combination treatment will continue receiving sorafenib at the dose of 400 mg bid alone. For patient treated in the combination therapy with a dose of sorafenib lower than 400 mg bid, dose escalation to sorafenib 400 mg bid will be made 2 weeks after the last infusion of vinorelbine, if criteria for retreatment are met.

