## 6. STUDY DESIGN

This will be a non-randomized, open label, phase I/II, multi-centre study of sorafenib in combination with fixed doses of vinorelbine as first-line treatment for women with metastatic breast cancer.

In the Phase I of the study, 6-12 patients will be recruited in a single center (Jewish General Hospital, Montreal).

In the Phase II part, 21-24 more patients will be recruited and treated in six different centers in Quebec.

The first part of the study will test increasing doses of sorafenib, combined with regular administration of vinorelbine at fixed therapeutic doses (30 mg per square meter on days 1 and 8 of 21-day cycles).

Dose escalations will be made in subsequent cohorts of patients, up to the recommended dose for sorafenib monotherapy. Sorafenib doses will be: 200 mg bid (cohort I) and 400 mg bid (cohort 2).

In the second part of the trial, the cohort of patients treated at the recommended dose will be expanded, up to a total of 27 patients treated with this schedule of the combination regimen (see Section 16.2).

Six patients treated at the recommended dose will be assessed for pharmacokinetic analysis.

Clinical follow-up, including physical examination, laboratory testing and evaluation of adverse event will be performed on day 1 and 8 of each cycle.

Patients will have appropriate radiological imaging to document baseline disease within 4 weeks prior to study entry. Radiological imaging will be repeated regularly after every two cycles, until disease progression or unacceptable toxicity, up to 8 cycles (or after at least 4 cycles after achievement of the best response obtained).

Those patients whose disease has not progressed during the combination treatment, will continue receiving sorafenib alone at the dose of 400 mg bid and will be monitored every 42 days, with clinical and radiological follow-up.

All patients will be followed for a minimum of 2 years for survival and residual toxicity.

Safety will be assessed by examination of adverse events, clinical laboratory data, and vital signs. Adverse events, use of growth factors, and changes in laboratory parameters will be summarized and tabulated. Objective response (CR, PR, SD, and PD) will be summarized and tabulated. Time to response, duration of response, time to progression, and survival will be calculated. Kaplan-Meier estimates and curves will be used to present these time-to-event data.

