## 11. TOXICITY AND DOSE DELAYS - MODIFICATIONS

### 11.1 Criteria for retreatment

If disease progression is not observed, patients will be retreated at the same dose level of cycle 1, unless a dose reduction is necessary as a consequence of toxicity, according to criteria listed below.

Hematological toxicity is expected to occur mainly as a consequence of treatment with vinorelbine.

In order to receive vinorelbine therapy, both on day 1 and 8 of each cycle, patients must have ANC  $\geq 1.0 \times 10^9/L$  and platelets  $\geq 75 \times 10^9/L$ .

No sorafenib interruption is mandatory in case of hematological toxicity.

In case of diarrhea, skin rash, hand-foot syndrome or hypertension, most probably attributable to sorafenib intake, the administration of vinorelbine will be allowed, at investigator's discretion.

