#### 11.4 Hand-foot skin syndrome (HFS)

As a consequence of treatment with sorafenib, patients may experience a reddening and soreness of the skin, particularly on the surfaces of the hand and feet but also in skin folds. This toxicity is referred to as hand-foot syndrome (HFS).

HFS will be graded as following:

- Grade 1: painless mild erythema, swelling, or desquamation nor interfering with daily activities;
- Grade 2: painful erythema, desquamation, or swelling interfering with, but not precluding normal physical activities; or small blisters or ulcerations less than 2 cm in diameter;
- Grade 3: blistering, ulcerations, swelling or severe pain interfering with walking or performing normal daily activities; cannot wear regular clothing;
- Grade 4: diffuse or local process causing serious infectious complications, or a bedridden state or hospitalization.

Patients will be provided recommendations to decrease its incidence and severity.

In the presence of Grade  $\geq 2$  HFS, patients must be aware of the need to hold sorafenib intake, until resolution to Grade  $\leq 1$  HFS.

A dose level decrease (see Section 12.8) will be applied for patients presenting Grade 3-4 HFS, or two separate episodes of Grade 2 HFS with an interval shorter than 3 months.

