## 11.9 Dose modifications

No intra-patient dose escalation for sorafenib will be allowed during the combination with vinorelbine.

Any patient experiencing at any cycle a toxicity requiring a dose reduction, will be evaluated by the investigator, who will evaluate the risks for the patient to restore therapy and the utility of continuing the study treatment at lower doses, rather than definitively terminating her participation in this trial. The investigator must be aware of the multiple therapeutic possibilities that are usually available for patients at this stage of disease.

Patients experiencing vinorelbine-induced toxicities requiring a dose reduction will be treated at a dose of 25 mg/m^2, and then 20 mg/m^2, if a second dose reduction is necessary. No further dose reductions will be allowed.

Sorafenib dose reduction is mandatory for patients experiencing a DLT (see Section 12), and recommended for patients experiencing the need of frequent drug suspensions (>twice in 2 months). Sorafenib dose can be lowered from 400 mg bid to 200 mg bid, and from 200 mg bid to 200 mg qd (up to a maximum of two dose-reductions for patients treated in cohort 2 dose level).

If a patient undergoes sorafenib dose reduction(s) during combined treatment with vinorelbine, the same dose will be maintained as monotherapy treatment, in the absence of progressive disease after completion of chemotherapy.

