## 12. DEFINITION OF DOSE-LIMITING TOXICITY (DLT)

Dose-limiting toxicity is defined as one or more of the following:

- 1) Febrile neutropenia, defined as a temperature  $\geq 38.5^{\circ}\text{C}$  in the presence of ANC  $< 1.0 \times 10^9/\text{L}$ .
- 2) Grade 4 neutropenia lasting more than 5 days.
- 3) Grade 4 thrombocytopenia ( $< 25 \times 10^9/\text{L}$ ) or anemia ( $< 65 \text{ g/L}$ ).
- 4) Grade 3 thrombocytopenia ( $< 50 \times 10^9/\text{L}$ ), if lasting more than 5 days.
- 5) Grade 3 AST-ALT increase ( $> 5.0 \times \text{ULN}$ ), if lasting more than 5 days.
- 6) Grade 3 rash, if lasting more than 5 days after suspension of sorafenib.
- 7) Grade 3 diarrhea, if lasting more than 24 hours from suspension of sorafenib and adequate treatment with loperamide or diphenoxylate/atropine.
- 8) Other non-hematological toxicity of Grade  $\geq 3$ , except unpremedicated nausea or vomiting, vinorelbine-induced peripheral phlebitis or extravasation ulceration.
- 9) Impossibility to start the second cycle of therapy within 14 days from the planned day, as a consequence of toxicity.

Any patient experiencing a DLT at any cycle will be evaluated by the investigator, who will assess the utility for the patient of continuing the study treatment at lower doses, rather than definitively terminating his participation to this trial.

No patient experiencing a DLT will be retreated at the same dose. The investigator will evaluate risks and benefits for the patient, being aware of the multiple therapeutic possibilities that are usually available for patients at this stage of disease.

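### Sections 6 and 9.5 set sorafenib monotherapy at 400 mg bid without exempting patients reduced for toxicity; for reductions without a DLT, only Section 11.9 says otherwise

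*Protocol*

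**What the plan says.** Three places in the protocol set the sorafenib dose after combination therapy.

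- **Section 6** says that patients who have not progressed "will continue receiving sorafenib alone at the dose of 400 mg bid". It names no exception.
- **Section 9.5** repeats the 400 mg bid rule. For patients who received less than that in combination, it adds that "dose escalation to sorafenib 400 mg bid will be made 2 weeks after the last infusion of vinorelbine, if criteria for retreatment are met".
- **Section 11.9** says: "If a patient undergoes sorafenib dose reduction(s) during combined treatment with vinorelbine, the same dose will be maintained as monotherapy treatment", provided the disease has not progressed.

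Two other places bear on the question. Section 11.1, headed as the criteria for retreatment, returns patients to the cycle 1 dose level "unless a dose reduction is necessary as a consequence of toxicity, according to criteria listed below". Section 12 says "No patient experiencing a DLT will be retreated at the same dose".

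**The concern.** A patient who started at 400 mg bid, was reduced to 200 mg bid for toxicity and has not progressed falls under both Section 9.5 and Section 11.9. The first raises her dose to 400 mg bid and the second keeps it at 200 mg bid. No text ranks the sections, and neither Section 6 nor Section 9.5 mentions Section 11.9.

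A centre that takes the monotherapy dose from Section 9.5 can therefore put a patient back on a dose she did not tolerate, while a centre that reads Section 11.9 will not. Phase II runs in six centres, and according to Section 4 the combination had not been tested in humans before.

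**Working it through.** The protocol gives no figure to reproduce here. The check is a comparison of the rules, plus the dose arithmetic.

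**1. Whom Section 9.5 escalates.** The group is anyone whose combination dose was below 400 mg bid. It includes patients assigned 200 mg bid (cohort 1, or a recommended dose of 200 mg bid) and also patients reduced from 400 mg bid. The text does not separate them.

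**2. Whether the condition in Section 9.5 excludes reduced patients.** Escalation requires that retreatment criteria are met, which leads to Section 11.1. The explicit thresholds there begin "In order to receive vinorelbine therapy, both on day 1 and 8 of each cycle, patients must have ANC" and go on to require ANC of at least 1.0 × 10⁹/L and platelets of at least 75 × 10⁹/L. They concern vinorelbine. A patient whose skin toxicity has resolved can meet them. The clause on necessary dose reductions in the same section is framed against the cycle 1 dose and does not mention monotherapy.

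**3. Whether the ban on intra-patient escalation in Section 11.9 helps.** It covers only the period of combination with vinorelbine, so it has ended when Section 9.5 applies.

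**4. Which reductions Section 12 also covers.** Section 12 bars a return to the same dose, but only after a DLT. Item 8 begins "Other non-hematological toxicity of Grade" and covers Grade 3 or higher, with listed exceptions.

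| Reason for sorafenib reduction | Reduction rule | DLT under Section 12? | What opposes 400 mg bid |
|---|---|---|---|
| Grade 3 hand-foot syndrome | 11.4 | Yes, item 8 | 11.9 and 12 |
| Grade 3 hypertension | 11.6 | Yes, item 8 | 11.9 and 12 |
| Grade 3 diarrhea beyond 24 hours despite suspension and treatment | 11.3 | Yes, item 7 | 11.9 and 12 |
| Grade 3 rash beyond 5 days after suspension | 11.5 | Yes, item 6 | 11.9 and 12 |
| Two Grade 2 hand-foot episodes within 3 months | 11.4 | No | 11.9 only |
| Second Grade 3 rash within 3 months, 5 days or less | 11.5 | No | 11.9 only |
| Grade 3 AST/ALT rise of 5 days or less, possibly related to sorafenib | 11.8 | No, item 5 needs more than 5 days | 11.9 only |
| More than two suspensions in 2 months (reduction recommended, not mandatory) | 11.9 | No | 11.9 only |

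The entries for DLTs assume that the DLT occurred at 400 mg bid. The four non-DLT rows are examples and not a complete count. Section 11.4, for instance, sets the hand-foot trigger as "or two separate episodes of Grade 2 HFS with an interval shorter than 3 months", and Section 11.8 also lets the investigator modify treatment for recurrent Grade 2 toxicity.

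**5. Size of the dose difference.**

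- 400 mg bid: 2 × 400 = 800 mg/day
- 200 mg bid: 2 × 200 = 400 mg/day
- 200 mg qd: 200 mg/day
- After one reduction from 400 mg bid: 800 / 400 = 2-fold
- At 200 mg qd: 800 / 200 = 4-fold

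**6. Whether cross-references lead the reader to Section 11.9.** The sorafenib reduction rules in Sections 11.3 to 11.6 point to Section 12.8, which does not exist. Section 6.1 shows an offset of one section number: it cites 8 and 9 for eligibility criteria that stand in 7 and 8. The same correction turns 12.8 into 11.8, which covers other toxicities, and not into 11.9.

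**The case against.** The strongest answer is that the specific rule governs the general one. Section 6 is a design summary and Section 9.5 concerns duration. Section 11.9 is the section on dose modifications and describes exactly this patient. If Section 9.5 is read as covering only patients assigned 200 mg bid, both sections have work to do; otherwise the last rule in Section 11.9 has little effect. The reference in Section 9.5 to retreatment criteria, together with the clause on necessary dose reductions in Section 11.1, can be read the same way.

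This stands as the likely intent. It does not remove the conflict, because Section 9.5 is itself specific: it addresses patients below 400 mg bid and tells the centre to escalate them. A recovered patient can meet the one condition it sets.

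A second answer is that safeguards remain. Section 10.2 keeps 21-day visits for the first 8 monotherapy cycles, Sections 11.3 to 11.6 contain rules for holding sorafenib, and Section 14 lets the investigator stop treatment at any time. These limit harm after a wrong escalation but do not prevent it. Visits also become less frequent at the switch, from days 1 and 8 of each cycle to day 1 only.

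A third answer is that the Section 12.8 pointers are a numbering slip. That is fair. They are clerical and do not show that a centre would misdose. They only make Section 11.9 harder to find.

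**Conclusion.** The conflict is real and should be fixed. Followed as written, Section 9.5 can return a patient to the dose from which she was reduced, at 2 or 4 times the daily dose that Section 11.9 gives her. For reductions without a DLT, Section 11.9 is the only rule that sets a lower monotherapy dose.

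A reader might infer more than this, and the protocol does not support it:

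- **That reduced patients have no protection.** Section 11.9 protects all of them on its face, and Section 12 adds protection after a DLT at 400 mg bid.
- **That centres will dose differently.** The text permits it, but the probable intent is Section 11.9 and many investigators may read it so.
- **That a number of patients can be given.** The protocol states no rate for reductions without a DLT, so none is claimed.
- **That the statistical design is affected.** The sample size of 27 and the binomial test in Section 16.1 do not depend on the monotherapy dose rule.

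The conclusion rests on the wording of the protocol and on no numerical assumption.

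**What to change.** In Sections 6 and 9.5, limit escalation to 400 mg bid to patients who were assigned a lower dose by cohort or recommended dose and had no toxicity-related sorafenib reduction. State in both places that Section 11.9 governs every reduced patient. Change the Section 12.8 pointers to Section 11.9.

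Two unrelated mismatches can be cleaned up in the same amendment:

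- **Wait after radiation.** The minimum is 8 days in Section 13.1 and 15 days in Section 14. Using 15 satisfies both.
- **Day-1 postponements before G-CSF is allowed.** Section 11.2 can be read as one or two, and Section 13.4 says three. Using three satisfies both, since G-CSF is allowed and not required.

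The cost is one clause in each of two sections plus corrected pointers and these two values, sent to all centres with the ethics approvals that Section 19.1 requires for amendments. Sample size, data collection and analysis do not change.

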### 10. PATIENT ASSESSMENT

#### 10.1 Screening procedures

All patients will have blood tests and urinalysis within two weeks from therapy start.

Within 4 weeks prior to therapy start, patients will have appropriate radiological imaging to document baseline disease, according to RECIST criteria, for targeted lesions (see Appendix E), including a bone scan and a baseline chest x-ray (unless CT or MRI scans of the thorax are performed) and an abdomen ultrasound (unless CT or MRI scans of the abdomen are performed). Brain CT or MRI scans are only required in the presence of

symptoms suggestive for CNS involvement.

Within 4 weeks prior to therapy start, patients will have appropriate cardiac evaluation, by either multigated acquisition (MUGA) scan or echocardiogram (ECHO) and 12-lead ECG.

Past and present medical/oncological history including concomitant medications, physical examination, signs and symptoms and ECOG performance status will be assessed within two weeks from therapy start.

Patients with difficult peripheral venous access should be proposed to have the placement of a central access device, followed by complete wound healing before therapy start.

Once the eligibility of a patient is confirmed, the informed consent will be signed both by the investigator proposing the participation to the trial, and by the patient.

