## 7. INCLUSION CRITERIA

Patients meeting the following criteria will be eligible for enrollment:

1. Women affected by histologically proven metastatic breast cancer.
2. Tumor not susceptible to therapy with trastuzumab, defined as FISH negative for HER-2 amplification or immunohistochemistry 0-1+ for HER-2 expression.
3. Female, age  $\geq 18$ .
4. Documented measurable disease by appropriate radiologic imaging according to RECIST criteria (see Appendix E). Lesions in previously irradiated areas are not considered measurable disease, unless progression has been documented post-radiation.
5. ECOG performance status 0-1 (see Appendix B).
6. Life expectancy  $> 6$  months.
7. Adequate bone marrow function, as indicated by:
  - hemoglobin  $\geq 90$  g/L;
  - neutrophils  $\geq 1.5 \times 10^9/L$ ;
  - platelets  $\geq 100 \times 10^9/L$ .
8. Adequate renal function, as indicated by serum creatinine  $\leq 1.5$  times the upper limit of normal and/or Creatinine Clearance calculated as  $>50\%$  lower normal limit, or estimated as  $\geq 50$  ml/min (Appendix C).
9. Adequate liver function, as indicated by:

- bilirubin  $\leq 1.5$  times upper normal limit;
- AST and ALT  $\leq 2$  times upper normal limit.
- 10. Left ventricular ejection fraction (LVEF)  $\geq 50\%$  as measured by either multigated acquisition (MUGA) scan or echocardiogram (ECHO).
- 11. No therapy for breast cancer in the 4 weeks preceding the therapy start.
- 12. Women of childbearing potential must be using adequate contraception and have a negative pregnancy test at the time of enrollment.
- 13. Patient able to understand and give written informed consent.

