## 8. EXCLUSION CRITERIA

Patients are excluded from the study if any of the following criteria is met:

1. Patients with locally advanced breast cancer or stage IIIb only.
2. Presence of only non-measurable disease.
3. Previous (neo)adjuvant chemotherapy with vinorelbine.
4. Any previous anti-angiogenic therapy.
5. Any previous chemotherapy for metastatic breast cancer. Previous hormonal treatments or radiotherapy for metastatic disease are allowed.
6. Radiotherapy, chemotherapy or hormonal therapy for breast cancer in the last 4 weeks prior to starting the study treatment.
7. Major surgery within 4 weeks of first study treatment, or minor surgery (including placement of an access device) within 7 days of therapy start.
8. Presence of life-threatening disease or central nervous system localizations.
9. Evidence of HER-2 positive breast cancer, defined as FISH-positive for amplification or score 3+ by immunohistochemistry.
10. Any other possibly active primary tumor, except basal cell carcinoma of the skin, or carcinoma in situ of the cervix.
11. Clinically significant hepatic disease with respect to hepatitis B, hepatitis C, cirrhosis or other liver diseases.
12. Uncontrolled bacterial, viral or fungal infection.
13. Previous history of ischemic disease.
14. Patients with previous history of thrombo-embolic events, or with documented risk factors for thrombotic disease other than cancer.
15. History of gross hemorrhage within the past 6 months (e.g., hemoptysis or hematuria requiring medical intervention).
16. Uncontrolled hypertension.
17. Other serious medical conditions, such as uncontrolled cardiac disease, severe pulmonary disease, uncontrolled diabetes.
18. Patient exhibiting confusion or disorientation.
19. Any condition (medical, psychological, geographical) that would prevent adequate follow-up.
20. Patient is pregnant, or is breast-feeding, or is unwilling to use adequate contraception.
21. Failure to give informed consent.

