**Questions to:**  
DSI [contact]

If the report is made via telephone, a written report must follow as soon as possible, which includes a full description of the event and any sequelae. SAEs that occur at any time after the inclusion of the subject in the study (defined as the time when the subject signs the informed consent) up to 30 days after the subject completed or discontinued the study must be reported.

The subject is considered to have completed the study either after the completion of the last visit or contact (eg, phone contact with the investigator), or after the last dose of study medication, whichever is later.

The date of discontinuation is when a subject and/or investigator determines that the subject can no longer comply with the requirements for any further study visits or evaluations (e.g. the subject is prematurely discontinued from the study).

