## **19.3 Subject information and consent**

All parties will ensure protection of subject personal data and will not include subjects names on any sponsor forms, reports, publications, or in any other disclosures. In case of data transfer, Bayer will maintain high standard of confidentiality and protection of subject personal data.

The informed consent form, or any change made during the course of the trial, must be prospectively approved by the IRB/IEC of each participating center.

The responsible investigator in each center must ensure that each trial subject, or her legally acceptable representative, is fully informed about the nature and objectives of the trial and possible risks associated with participation.

The investigator, or a person designated by the investigator, will obtain written informed consent from each subject or the subject's legally acceptable representative before any trial-specific activity is performed (screening evaluations are not considered as trial-specific). The investigator will retain the original of each subject's signed consent form.

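### Consent is signed only after eligibility is confirmed, and all screening is exempt from it, so protocol-required tests can precede written trial consent and serious events from them fall outside safety reporting

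*Protocol*

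**What the plan says.** Five places in the protocol bear on when consent is given and what depends on it.

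- **Section 10.1 (Screening procedures)** sets out the tests. Urinalysis, blood tests, history and examination fall within two weeks of starting therapy. RECIST baseline imaging (including a bone scan), MUGA or echocardiogram, and a 12-lead ECG fall within four weeks. It adds that "Patients with difficult peripheral venous access should be proposed to have the placement of a central access device". The last sentence of the section gives the order: "Once the eligibility of a patient is confirmed, the informed consent will be signed". It names two signatories, the investigator and the patient.
- **Section 19.3 (Subject information and consent)** requires written consent from the patient or a legally acceptable representative before trial-specific activity, then adds in parentheses that "screening evaluations are not considered as trial-specific".
- **Sections 7 and 8** put consent among the entry criteria. Inclusion 13 reads "Patient able to understand and give written informed consent"; exclusion 21 reads "Failure to give informed consent".
- **Section 15.5** starts SAE reporting at inclusion in the study, "defined as the time when the subject signs the informed consent".
- **Section 16.6** starts AE reporting at the first study drug.

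**The concern.** The order in 10.1 conflicts with the entry criteria: eligibility includes having given consent, yet the signature comes after eligibility is confirmed. The more serious matter is the exemption in 19.3. It is not limited to tests that a patient would have had anyway. It therefore covers a cardiac scan done to apply this trial's LVEF cut-off, or imaging repeated because an existing scan is older than the trial's window.

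Two things are at stake. The first is participant protection. Section 19.2 commits the trial to the Declaration of Helsinki, and the text in Appendix A says that potential subjects are to be told about a study's aims, methods and hazards. Under 10.1 and 19.3 a woman can complete all protocol screening before she has signed for the trial. The second is safety capture: both reporting windows open after screening, so a serious event caused by a protocol-required test has no stated reporting route if it occurs before signature.

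**Working it through.** The plan gives no figure on this point and no statistical calculation applies. The check is to put the rules in sequence and see what each permits.

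1. **Must screening precede confirmation of eligibility?** Yes. Inclusion 10 needs an LVEF of at least 50% by MUGA or echocardiogram, inclusion 4 needs measurable disease on imaging, and inclusions 7 to 9 need laboratory values. None of these can be judged before the tests are done. Section 6.1 likewise registers a patient only after the pretreatment procedures are complete and all criteria have been reviewed.
2. **Must confirmation precede signature?** Yes, by the closing sentence of 10.1.
3. **Is signature itself part of eligibility?** Through exclusion 21, yes. Inclusion 13 is weaker, since it concerns the patient's ability to consent and not the act. The conflict with step 2 therefore rests mainly on exclusion 21.
4. **Does any other section require consent before screening?** No. Section 19.3 is the only general consent rule, and its parenthesis removes screening from it without distinguishing routine from protocol-driven tests.
5. **When do the reporting windows open?** The SAE window opens at signature (15.5) and the AE window at first drug (16.6).

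The sequence that follows is:

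protocol-required screening → eligibility confirmed → consent signed (SAE window opens) → first study drug (AE window opens)

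An SAE in the first stretch is in neither window. One that first occurs after signature is covered by 15.5, even if a screening test caused it.

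**Length of the gap.** Imaging and cardiac tests may be up to 4 weeks before therapy, so 4 × 7 = 28 days. Urinalysis and blood tests may be up to 2 weeks before, so 2 × 7 = 14 days. Both are maxima measured back from first dose. The unreported interval is shorter by the time between signature and first dose, which the protocol does not state.

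**Number of patients.** Section 6 plans 6–12 patients in Phase I and 21–24 more in Phase II, so 6 + 21 = 27 to 12 + 24 = 36 enrolled. Screen failures come on top, and the protocol does not estimate them. The rule applies to all of them. How many will have a test done only because of the protocol cannot be derived from the document.

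**Who may consent.** Section 19.3 accepts a legally acceptable representative. Inclusion 13 requires that the patient herself can understand and consent, exclusion 18 removes patients with confusion or disorientation, and 10.1 has the patient sign. These do not agree.

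**The case against.** The strongest reply is that 10.1 and 19.3 agree with each other. Both treat screening as ordinary work-up and put consent after it, and each centre's ethics board must approve that (19.1). A workable order exists: screen, check the clinical criteria, sign, which settles exclusion 21, then register and treat. This stands. A reader might infer from the wording that the order is impossible to follow, and the documents do not support that. What remains is loose wording in 10.1 and an exemption in 19.3 that is wider than ordinary work-up.

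Other stronger readings also fail:

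- **The central access device.** A reader might take it as an invasive research procedure done before consent. Section 10.1 only says that it should be proposed, with healing before therapy starts, so placement after signature is possible. It is not plainly a screening evaluation, so the 19.3 exemption may not reach it. Section 2.2 describes central administration as preferable whenever peripheral access is difficult. Section 15.4 also takes hospitalisation solely for placing a permanent catheter out of the SAE definition, whatever the consent date.
- **Coagulation, lipase and amylase at screening.** The schedule table is broken in the text available, so its screening column cannot be read. Only the tests named in 10.1 are relied on here.
- **Research-only radiation for every patient.** LVEF may be measured by echocardiogram, chest x-ray and ultrasound are waived if CT or MRI is done, and some imaging will be routine staging. The protocol permits unconsented protocol-driven tests; it does not show that every patient has one.
- **Unusable baseline data.** Nothing in the protocol says that screening results obtained before consent would be lost. That is speculation.

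It can also be said that 15.1 ties adverse events to study treatment, so a first-drug start in 16.6 is coherent. That is fair for 16.6. It does not answer 15.5, which opens at signature, before any drug, and so evidently means to capture serious events before dosing.

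**Conclusion.** The point holds in a limited form. Section 10.1 and exclusion 21 are inconsistent on whether consent comes before or after eligibility is confirmed. The unqualified exemption in 19.3 lets protocol-required, trial-timed screening go ahead without written trial consent. A serious event from that screening before signature is in neither reporting window.

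The rule reaches every screened patient, with a gap of at most 28 days for imaging and cardiac tests and at most 14 days for urinalysis and blood tests. The conclusion assumes that sites follow the text literally. Here, without consent means without written consent to the trial; ordinary clinical consent to a procedure is not ruled out. No effect on the primary endpoint, sample size or analysis is shown. This is a participant-protection and safety-capture defect that should be corrected because it is cheap to correct. The representative wording in 19.3 is a separate and smaller inconsistency.

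**What to change.** - **Section 10.1:** replace the closing sentence with a requirement that the patient gives written consent before any screening procedure done because of the protocol. State that results of procedures already done as routine care may be used if they fall within the existing windows.
- **Section 19.3:** delete the parenthesis "screening evaluations are not considered as trial-specific", or limit it to procedures done as routine care.
- **Section 15.5:** no change is needed. Its clock runs from signature and will then cover protocol-driven screening. Routine tests done earlier stay outside it, which is appropriate. To keep sites consistent, 10.1 could require the site to record which screening results came from routine care.
- **Representative consent:** reconcile 19.3 with inclusion 13 and with the patient signature required in 10.1.

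The cost is an amendment to the wording. Consent is taken somewhat earlier, by up to 4 weeks at most, and some patients who then fail screening will have signed. No procedure, sample size or analysis changes.
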